## Abstract

**Background:**

Many university students experience mental health problems such as anxiety and depression. To support their mental health, a transdiagnostic mobile app intervention has been developed. The intervention provides short exercises rooted in various approaches (eg, positive psychology, mindfulness, self-compassion, and acceptance and commitment therapy) that aim to facilitate adaptive emotion regulation (ER) to help students cope with the various stressors they encounter during their time at university.

**Objective:**

The goals of this study are to investigate whether the intervention and its components function as intended and how participants engage with them. In addition, this study aims to monitor changes in distress symptoms and ER skills and identify relevant contextual factors that may moderate the intervention’s impact.

**Methods:**

A sequential explanatory mixed methods design combining a microrandomized trial and semistructured interviews will be used. During the microrandomized trial, students (N=200) will be prompted via the mobile app twice a day for 3 weeks to evaluate their emotional states and complete a randomly assigned intervention (ie, an exercise supporting ER) or a control intervention (ie, a health information snippet). A subsample of participants (21/200, 10.5%) will participate in interviews exploring their user experience with the app and the completed exercises. The primary outcomes will be changes in emotional states and engagement with the intervention (ie, objective and subjective engagement). Objective engagement will be evaluated through log data (eg, exercise completion time). Subjective engagement will be evaluated through exercise likability and helpfulness ratings as well as user experience interviews. The secondary outcomes will include the distal outcomes of the intervention (ie, ER skills and distress symptoms). Finally, the contextual moderators of intervention effectiveness will be explored (eg, the time of day and momentary emotional states).

**Results:**

The study commenced on February 9, 2023, and the data collection was concluded on June 13, 2023. Of the 172 eligible participants, 161 (93.6%) decided to participate. Of these 161 participants, 137 (85.1%) completed the first phase of the study. A subsample of participants (18/172, 10.5%) participated in the user experience interviews. Currently, the data processing and analyses are being conducted.

**Conclusions:**

This study will provide insight into the functioning of the intervention and identify areas for improvement. Furthermore, the findings will shed light on potential changes in the distal outcomes of the intervention (ie, ER skills and distress symptoms), which will be considered when designing a follow-up randomized controlled trial evaluating the full-scale effectiveness of this intervention. Finally, the results and data gathered will be used to design and train a recommendation algorithm that will be integrated into the app linking students to relevant content.

**Trial Registration:**

ClinicalTrials.gov NCT05576883; https://www.clinicaltrials.gov/study/NCT05576883

**International Registered Report Identifier (IRRID):**

DERR1-10.2196/46603

## Introduction

### Background

For young people, the years at university coincide with a transitional period of emerging adulthood [1,2]. This period is not only exciting but also a demanding and uncertain phase in life, and for some, it poses a great risk to their psychological well-being. Globally, it is estimated that between 12% and 50% of all university students are affected by mental health (MH) problems [3-5], the most common ones being anxiety, depression, and substance abuse disorder [3,4,6]. Because of the increased demands for MH support, traditional means of providing it, such as in-person counseling services, are difficult to achieve [7]. Even before the COVID-19 outbreak, which imposed additional challenges to student well-being [8,9], college counseling centers reported that they needed to continually adjust their operations to meet the demands for students’ MH needs [10]. In-person MH support also does not fully fit the needs of all students. In fact, students who experience increased MH problems are especially less likely to seek help, and informal and web-based resources are preferred [11]. Moreover, students who experience higher levels of MH-related stigma are less inclined to use face-to-face MH services and are more open to digital tools such as MH mobile apps [12].

To help students navigate this transitional period of their life and equip them with skills relevant for and beyond university life, it is vital to develop preventive and therapeutic interventions that are easily accessible, can counteract MH-related stigma, and are at the same time cost-effective [13]. As part of a student well-being program introduced at Erasmus University Rotterdam (EUR) in 2019, a mobile app consisting of preventive self-guided MH tools is being developed. Its goal is to help students better manage their MH by supporting them in the development of adaptive emotion regulation (ER) strategies.

Digital tools supporting MH have been proven to be good solutions for existing barriers to care, such as long waiting lines and MH-related stigma, owing to their accessibility and ability to maintain students’ privacy [14-16]. However, there are often substantial problems with the uptake (ie, use and acceptance) and actual effectiveness of these tools. Specifically, if the tool is not used for a recommended period, it is unlikely that it will have the intended effect [17,18]. Low uptake of interventions is often the result of a mismatch between technology and end users’ needs [19]. Technology offers countless possibilities for its use, but if a product is not developed in line with the target user’s needs (eg, values, goals, and abilities) or is not engaging and intuitive to use, the likelihood of such a product being integrated, accepted, and adopted by people is low [14,20]. Therefore, it is important to adopt user-centered eHealth design approaches, where the end user is involved across all stages of the design and development of the intervention as informant or co-designer and has a direct influence on both the outcome and the design process [21]. It is also essential to build a deeper understanding of how an intervention and its components function and under what circumstances they can be most beneficial for different users. This understanding can be helpful to tailor digital interventions to different types of users, optimizing their therapeutic benefits.

This paper describes the protocol for the optimization of a mobile app designed to improve students’ MH, combining a microrandomized trial (MRT) [22,23] with semistructured interviews. The goals of this study are to examine whether the intervention and its separate categories (ie, groups of exercises rooted in different therapeutic approaches supporting ER) have the intended effects and how students engage with and perceive them. In addition, relevant contextual factors, such as emotional state and the time of day, that may have an influence on intervention effectiveness will be explored. The latter will support the development of the prototype of a recommendation system that will connect students to the relevant content in the app based on their needs and characteristics. Ultimately, the study results will support the optimization and further development of this mobile app, which will later be evaluated for its overall effectiveness in a randomized controlled trial (RCT).

### MH Apps for University Students

The current generation of university students, consisting of millennials (those born between 1981 and 1996) and Generation Z (those born between 1997 and 2012), are considered digital natives. Research shows that these generations have developed specific behavioral characteristics owing to the influence of technology on their upbringing; for example, they communicate predominantly through web-based platforms, such as social media networks, because this provides quick and instant delivery of information [24]. This preference is not surprising, given that both young millennials and Generation Z highly value efficiency and the ability to perform multiple tasks at the same time [25]. These generations are digitally connected socially as well as informationally. They grew up in a society where information is instant and easily accessible, which in turn makes them prone to using more flexible learning methods and settings [25]. This explains why learning with the help of internet-based digital systems, such as games or mobile apps, attracts them [26]. Considering this generation’s needs and behavioral characteristics, interventions delivered through mobile phones are a good fit.

Several systematic reviews and meta-analyses have attested that digital interventions have the potential to improve mental well-being among this population [14,15,27-29]. However, most of the scientifically tested digital interventions for this population focus on web-based technologies and less so on mobile technology [14]. Mobile technology enables observation of the immediate context (eg, emotional state, location, and heart rate) through experience sampling and sensors and offers the possibility to recognize an individual’s needs and provide relevant support by using recommendation systems [30]. This permits greater precision in lending support at moments and under circumstances when an intervention is most useful and the person is receptive to it, which can play a crucial role in its uptake [30]. The fit between their needs and the delivered content was indicated to be an especially important feature among university students [18].

Despite the many advantages of digital technology in the field of MH, digital interventions struggle with low uptake and high attrition rates [31]. One of the main challenges is involving and keeping users engaged in the intervention over a longer time span [31,32]; for example, a study examining engagement patterns with trendy MH apps (≥10,000 downloads) found that user retention was only 3.9% two weeks after downloading the app [33]. The low uptake of digital MH interventions is considered one of the most potent barriers to beneficial effects on users’ MH because the intervention cannot have the potential impact when users do not engage with it [13]. Among university students, the main barriers to the use of MH apps include privacy concerns and concerns about the credibility of information. They prefer MH apps that are safe and secure, user friendly, credible, informative, and fitted specifically to their needs [13].

### The Mobile App for Students’ MH

#### Intervention Development

The development of the mobile app was guided by the Center for eHealth Research (CeHRes) road map, an established framework for the development of eHealth tools [19,34] in which evidence and theoretical insights are intertwined with design methods. This road map emphasizes a human-centered participatory design process and iterative approach to eHealth tool development [19]. Following this approach, the mobile app was designed with university students consistently at the center of the process and involved at all stages, from the analysis of the problem and context (ie, contextual inquiry) to the technical operationalization of the intervention. Students acted as informants and co-designers of the intervention. At the early stages of the intervention development, focus groups were conducted with other relevant stakeholders, that is, university psychologists and study advisors who are in close contact with this population. The development process involved a thorough review of scientific literature and multiple rounds of expert sessions involving MH professionals and behavioral scientists to lay a strong evidence- and theory-based foundation for our intervention. In collaboration with serious game and interaction designers, all intervention concepts and designs were tested with end users using qualitative and quantitative methods and iteratively adjusted in line with the results.

#### A Transdiagnostic Approach to MH

The intervention incorporates a transdiagnostic approach to MH (ie, Unified Protocol for Transdiagnostic Treatment of Emotional Disorders [35]) and implements techniques from various therapeutic approaches, such as positive psychology [36], mindfulness [37], acceptance and commitment therapy (ACT) [38], self-compassion [39], and cognitive behavioral therapy [40], to accommodate the diverse needs and content preferences of the student population. Using a transdiagnostic approach implies operating outside the traditional psychodiagnostics boundaries (ie, Diagnostic and Statistical Manual of Mental Disorders, Fifth Edition categories), focusing on the factors that cause or maintain problems that students present with. Instead of restrictedly following protocols aimed at specific disorders, this app will provide evidence-based interventions in a flexible fashion and in line with the needs and preferences of individual students [41].

Targeted psychological factors include negative self-referential thoughts, rumination, experiences of prolonged negative emotional states, and lack of MH literacy. These factors have been highlighted in the scientific literature [35,42-45] as well as by students, university psychologists, and study advisors interviewed at the start of this project. Targeting these transdiagnostic factors has been shown promising in the reduction of depressive and anxiety symptoms [35], both of which are prevalent among the university student population [3,4].

#### Intervention Structure

The current version of the mobile app consists of a suite of MH interventions in the form of short exercises. The goal of these exercises is to teach students how to use adaptive ER strategies such as acceptance, self-soothing, and reappraisal instead of maladaptive strategies such as avoidance, suppression, and rumination. In the short term, this will help them manage their emotional responses to internal (eg, unhelpful thoughts) or external (eg, failing a test) events by improving their ability to adjust or change the intensity and duration of emotional states [46]. In addition, students are frequently prompted to evaluate their emotional states through ecological momentary assessments (EMAs), which enable them to practice self-awareness and self-monitoring. In the long run, improving self-awareness and adopting adaptive ER strategies can work preventively by decreasing the likelihood of developing serious MH problems such as anxiety and mood disorders [47].

#### Our Vision for the Final Version of the App

For the final version of our MH app, we envision that students will be able to access multiple exercises at the same time and in any order and consume the content that is most relevant to their unique MH needs. Such a strategy has been previously proven successful in decreasing stress in university students in an Australian program for students called “thedesk” [48]. In addition, our app will include a recommendation system that will suggest exercises to students considering their unique characteristics, such as their goals, intervention preferences, MH state, momentary emotional state, the time of day, and individual app use history. The recommendation system introduces a potential solution to the low engagement and impact of the mobile intervention because efficiency, system responsiveness, and content relevance to users’ needs are highly valued among this population and have been reported as lacking in available MH apps [18,49].

#### Intervention Optimization Using an MRT Method

To design an adaptive system of interventions responsive to users’ needs, the optimization of their contents and delivery is crucial. This study will combine an MRT with user experience interviews, a novel study design that can provide information on which intervention is effective for whom and in what context [30].

An MRT can evaluate how different intervention components affect an individual in real time (ie, directly after they have used it), and it assesses how this effect varies over time (eg, an intervention may be effective at the beginning, but its effectiveness may decrease with time). In addition, this method can evaluate the moderating role of contextual factors (eg, current mood or the time of day) on the intervention effect, which is especially helpful when optimizing rules for intervention delivery [50,51]. Although it is a young method, an MRT has been successfully applied to evaluate dynamic and user-tailored eHealth interventions focused on weight management [52], smoking cessation [53], and MH [54]. Within the field of MH, NeCamp et al [55] investigated the optimal timing for delivering a mobile MH intervention to medical interns. The authors found that delivering an intervention when individuals experienced lower levels of MH indicated by low mood, poor sleep, and reduced activity was beneficial, whereas intervening when the individuals were doing well had a negative effect [55]. Another MRT study evaluated the impact of an ACT-based mobile intervention on distress symptoms (ie, depressive and stress symptoms) in first-generation university students [56], and the results suggest that interventions prompting mindful awareness and acceptance of internal experience (ie, thoughts, emotions, and physical sensations) were the most impactful for decreasing depressive symptoms. In addition, interventions delivered in the evening were more predictive of decreases in distress symptoms than those delivered in the morning [56]. Both studies signal the importance of considering contextual factors to optimize the impact of digital MH interventions.

Using MRT research design allows for the gathering of more granular and proximal insights about a given intervention, which cannot be captured through traditional RCT designs. In an MRT, unlike in a traditional RCT where individuals are randomized to an intervention or control group at the beginning of the trial, different intervention components (or no intervention) are repeatedly randomized to the participants at prespecified decision points. Thus, in an MRT, the randomization unit is not the participant but the intervention, and participants act as their own controls. Therefore, compared with an RCT, which focuses on between-participant effects, the MRT measures within-participant effects aggregated across participants. The decision point refers to the time of day at which an individual may or may not receive an intervention. Furthermore, the proximal outcome refers to the short-term goals of the intervention (ie, intervention targets) and is seen as the facilitator of the desired distal outcome of the intervention (ie, a mediator of the long-term outcome); for example, if the focus of an intervention is on increasing physical activity, a proximal outcome would be the number of steps taken within 30 minutes after an intervention was delivered, and the distal outcome would be the overall increase in physical activity at the end of the entire intervention period [51].

Finally, owing to repeated randomization, an MRT allows for the evaluation of the moderating role of contextual factors, such as current mood and time, on the proximal effects of the intervention [22].

### Study Objectives

This study combines an MRT design with semistructured user experience interviews to achieve the following research goals.

#### Evaluation of the Proximal Effects of the Intervention

This study will experimentally evaluate whether the intervention as a whole and its separate intervention categories (ie, groups of exercises categorized into 5 therapeutic approaches) have the intended effects on participants’ subsequent emotional states, which, in the long term, may have an impact on students’ MH (eg, depressive and anxiety symptoms) and acquisition of ER skills [47], and whether these effects deteriorate over time. Increases in positive affect and decreases in negative affect when an intervention is received compared with when a control intervention is received are expected and considered effective. For exercises targeting unhelpful thoughts (ie, cognitive defusion [CD]), changes in thought believability and discomfort with the thought before and after the exercises will be observed, and unhelpful thoughts are expected to subside as a result of exercise completion.

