**Figure 1 figure1:**
[figure not shown]
CONSORT (Consolidated Standards of Reporting Trials) flow diagram of participants’ progress through the mixed methods study integrating a microrandomized trial with semistructured interviews. EMA: ecological momentary assessment.

**Table 1 table1:** Overview of measurements performed during phase 1 (microrandomized trial).

	Day 1	Day 2 to day 22	Day 23
Emotional states		✓	
Thought believability and discomfort^a^		✓	
Demographics	✓		
Experience with MH^b^ apps	✓		
Knowledge of approaches	✓		
Use of MH techniques	✓		✓
Ten-Item Personality Inventory	✓		
General Health Questionnaire-12	✓		
Patient Health Questionnaire-9^c^			✓
Generalized Anxiety Disorder-7	✓		✓
Perceived Stress Scale-14	✓		✓
Emotion Regulation Skills Questionnaire	✓		✓

^a^Thought believability and discomfort are measured only before and after the cognitive defusion exercises.

^b^MH: mental health.

^c^The Patient Health Questionnaire-9 is part of the eligibility screening questionnaire; it is not readministered at baseline.

In phase 2, semistructured interviews will be conducted with a subsample of participants (21/200, 10.5%) investigating their user experience. The results of the qualitative phase will be used to interpret the quantitative results, obtaining a well-rounded picture of how the mobile intervention is functioning and its feasibility.

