### Outcome Measures

#### Primary Outcomes

##### Changes in a Momentary Emotional State

Participants will be asked to evaluate 7 emotional states by answering the question “How [*affect*, eg, happy] do you feel at the moment?” on a scale ranging from 1 (not at all) to 5 (very much). The emotional states are combined into 2 categories of affect: negative (stressed, frustrated, sad, and fatigued) and positive (happy, energetic, and relaxed) [98]. The scores of the emotional states will be averaged per category for preintervention and postintervention EMA assessment. The 2 composite outcomes will be calculated by subtracting the results of the preintervention EMA from those of the postintervention EMA for the positive affect and negative affect categories.

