##### Changes in Thought Believability and Discomfort

The CD exercises include a measure of thought believability and discomfort. Participants are asked to assess “How uncomfortable is the thought?” and “How believable (true) is the thought?” on a scale ranging from 1 (not at all uncomfortable or believable) to 100 (very uncomfortable or believable) [99] before and after they engage in the CD exercise.

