Every time participants fill in the preintervention EMA, they have a 60% chance of receiving an exercise and a 40% chance of receiving a health snippet. The 60:40 ratio was chosen to ensure a higher chance of receiving an intervention at every decision point. This strategy has been used in previous MRT studies too [51,52]. For this study, a simple randomization with replacement will be used. The randomization is carried out automatically within the app and is as follows:  randomization of exercise (60% chance) or control intervention; if an exercise is chosen, a second randomization to the intervention categories follows (20% chance for each intervention category), followed by the random selection of 1 exercise within the randomized intervention category (equal chance across exercises); if a control intervention is randomized (40% chance), a second randomization takes place in which a health information snippet is selected. Participants will be asked to complete 42 preintervention EMAs and 42 postintervention EMAs in total during the study. They can receive an exercise 0 times, 1 time, or maximally 2 times in a day. On average, they will be prompted to engage in 1.2 exercises per day and 25.2 exercises throughout the study.

Upon the completion of either the exercise or the control intervention, the participants are asked to reassess their emotional state by completing the postintervention EMA. When assigned to an exercise, in addition to the postintervention EMA, participants will be asked to rate the likability and helpfulness of the exercise. When CD exercises are selected, participants will also complete the corresponding measures of thought believability and discomfort before and after the exercise.

Given that the primary objective of this study is to evaluate the functioning of the intervention rather than observe it in a naturalistic setting, we have implemented an adherence protocol to enhance completion rates and ensure high-quality data. To support participants in staying engaged, they will receive emails or telephone calls from researchers, depending on the number of missed sessions. The adherence protocol is presented in Multimedia Appendix 3.

Immediately after the intervention period is concluded, participants will complete the postintervention assessment, including the secondary outcome measures (refer to Table 1 for an overview of the measurements performed during phase 1 of the study).

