##### Thought Believability and Discomfort Outcome

A multiple linear regression model will be applied to assess the effects of CD exercises on the level of thought believability and discomfort measured before and after CD exercise completion.

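### Thought believability and discomfort are rated only around cognitive defusion exercises, so the before-after change cannot support the causal wording that the protocol attaches to it

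*Protocol article*

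**What the plan says.** **Tier.** In Outcome Measures, the subsection on changes in thought believability and discomfort stands under the heading "Primary Outcomes", and its analysis stands under Primary Outcome Analysis. The abstract and Study Design name only emotional states and engagement as primary. Study Design gives the thought ratings a separate sentence.

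**Where measured.** Three places agree:
- Outcome Measures: "The CD exercises include a measure of thought believability and discomfort".
- Table 1, footnote a: "Thought believability and discomfort are measured only before and after the cognitive defusion exercises".
- Study Procedure, Phase 1: "When CD exercises are selected, participants will also complete the corresponding measures of thought believability and discomfort before and after the exercise".

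**What is concluded.** The objective on proximal effects says that "unhelpful thoughts are expected to subside as a result of exercise completion". The Data Analysis Plan states: "A multiple linear regression model will be applied to assess the effects of CD exercises on the level of thought believability and discomfort".

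**What is done for affect.** The same objective sets a comparative standard for the emotional states: "Increases in positive affect and decreases in negative affect when an intervention is received compared with when a control intervention is received are expected". The analysis plan tests this against the control intervention, overall and for each of the five categories.

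**The caveat.** The objective on distal outcomes says that, without a comparator, before-after results can only indicate a possible link with the intervention. Neither the thought-outcome sections nor the Limitations say this about the thought ratings.

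**The concern.** The strength of a microrandomised trial is that each occasion with an exercise can be compared with occasions randomised to the control. That works only for outcomes measured on both kinds of occasion. Believability and discomfort have no value after a health snippet or after an exercise from the other four categories. No choice of regression model can recover the missing contrast.

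What remains is a change between two ratings of an unhelpful thought, taken within a flow limited to 30 minutes. The thought may fade by itself. A thought that was unusually strong when first rated will tend to regress. Being asked twice, or guessing what the exercise is meant to do, may also lower the second rating. The planned analysis cannot separate any of these from an effect of the exercise.

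Two things are at stake. The first is a causal statement about CD and unhelpful thoughts that the design does not support. The second is the use described in the Discussion overview, where categories may be removed or redesigned partly on their proximal effects. CD is the only category with two additional proximal outcomes, both uncontrolled, and the mechanisms above would push both toward apparent benefit.

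**Working it through.** **1. Inputs from the protocol article**
- Decision points per participant: 42 (Phase 1: MRT)
- Probability of an exercise: 0.60; of a snippet: 0.40; of each category given an exercise: 0.20 (same section)
- Response to prompts: 70% (sample size paragraph)
- Completers of phase 1: 137 (Results)
- Significance level: .05 (sample size paragraph), taken here as two-sided

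**2. The article's own figure.** 42 × 0.60 = 25.2 exercises per participant and 2 × 0.60 = 1.2 per day. Both match the text.

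**3. Occasions that supply thought ratings**
- CD assigned: 25.2 × 0.20 = 5.04 per participant
- CD completed at 70%: 5.04 × 0.70 = 3.53 per participant, or 3.528 × 137 = 483 in all
- Snippets completed at 70%: 42 × 0.40 × 0.70 = 11.8 per participant, none with a thought rating

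**4. Chance of a significant fall when the exercises do nothing.** The article does not list the regression terms, so the test is taken as one of zero mean change, on per-person means. Let d be the non-specific drift in SDs of the change score, and ICC the within-person correlation of change scores. Both are assumptions.

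SE = √[(ICC + (1 − ICC)/3.53) / 137]

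For ICC = 0, 0.3 and 0.6 this gives SE = 0.0455, 0.0603 and 0.0722. Two-sided rejection probability:

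| Drift d | ICC 0 | ICC 0.3 | ICC 0.6 |
|---|---|---|---|
| 0 | 0.05 | 0.05 | 0.05 |
| 0.05 | 0.20 | 0.13 | 0.11 |
| 0.1 | 0.59 | 0.38 | 0.28 |
| 0.2 | 0.99 | 0.91 | 0.79 |
| 0.3 | 1.00 | 1.00 | 0.99 |

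**5. What a comparator would have done.** A simulation (137 participants, ICC 0.3, 4,000 runs) supposed that the same ratings were also taken at snippet occasions, with the same drift there. The CD-versus-snippet contrast rejected in 0.04 to 0.05 of runs at every drift from 0 to 0.3. The uncontrolled test rejected in 0.04, 0.12, 0.33, 0.87 and 1.00 at drifts of 0, 0.05, 0.1, 0.2 and 0.3.

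**6. How large could drift be?** Take regression to the mean alone. If the thought is first rated s SDs above its usual level and the two ratings correlate at r, the expected fall is s(1 − r) rating SDs. The SD of the change is √[2(1 − r)] rating SDs, so d = s√[(1 − r)/2]. With one observation per participant, z = d√137. For r from 0.9 to 0.5:

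| Elevation s | d | z |
|---|---|---|
| 0 | 0 | 0 |
| 0.25 | 0.06 to 0.13 | 0.65 to 1.5 |
| 0.5 | 0.11 to 0.25 | 1.3 to 2.9 |
| 1 | 0.22 to 0.50 | 2.6 to 5.9 |

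The result depends on s as much as on r, and the article gives neither.

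**The case against.** The strongest reply has four parts.

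**A false positive is not assured.** A reader might infer that a fall would appear whatever the exercises do. The article does not support that. With zero drift the error rate is nominal, and an elevation of 0.25 SD gives z below 1.96 throughout the range above. CD is drawn at random whatever state the participant reports, so CD occasions are not selected for high distress. Any elevation must come from which thought the participant picks, and the article does not describe that. This part stands, and it limits the conclusion to what could happen.

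**Primary status is ambiguous.** The abstract and Study Design leave the thought ratings out of the primary outcomes, and the Bonferroni divisor of 2 matches the two affect composites. The heading in Outcome Measures still includes the ratings. This stands as a reason not to rest the point on tier. The causal wording is unsupported in any tier.

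**The wording is mild.** The objective says that changes will be observed and states an expectation, which can be read as a directional hypothesis. The same sentence nevertheless names the exercise as the cause, and the analysis plan sets out to "assess the effects of CD exercises on the level of thought believability and discomfort measured before and after CD exercise completion". A condensed article may leave out model terms, but no term can supply a control that was never measured.

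**CD already has a randomised test.** The analysis plan compares each category with the control on affect. The Discussion overview acts only on combined evidence: poor perception or low use together with a negative or absent proximal effect. A reader might infer that the thought ratings would override the randomised contrast. Nothing in the article says so. Nothing excludes their influence either, because the objectives list them among the proximal effects.

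**Conclusion.** The point holds in a limited form. Believability and discomfort have no control in this design, the objectives and the analysis plan nevertheless attribute their change to CD exercises, and the caveat given for the distal outcomes is missing here. Followed as written, the plan yields a causal conclusion that the data cannot carry.

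The size of the risk is conditional. With 137 participants and no true effect, the chance of a significant change is nominal at zero drift, 0.28 to 0.59 at 0.1 SD and 0.79 to 0.99 at 0.2 SD, for ICC from 0.6 to 0. These figures assume 70% response, a two-sided 5% level and a test of mean change. The drift, ICC, elevation and correlation are assumptions.

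The defect is confined to the two thought outcomes. The effect of CD on positive and negative affect keeps its randomised control.

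**What to change.** Data collection has ended, so the remedy lies in wording and interpretation:

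1. In the objective on proximal effects and in the analysis section for the thought outcomes, replace the causal wording with change from before to after CD exercises. Report that change as descriptive.
2. Attach the same no-comparator caveat that the distal outcomes carry, and repeat it in the Limitations.
3. State that any decision on keeping, redesigning or removing CD relies, for proximal effect, on the CD-versus-snippet contrast for positive and negative affect that is already planned.
4. Optionally, add a comparison among the six CD exercises, which are drawn with equal chance, adjusted for the rating before the exercise. Label it exploratory, because it answers a different question and has limited power. With 483/6 ≈ 81 flows per exercise, an assumed SD of 20 and r = 0.7, and flows treated as independent, the residual SD is 20 × √(1 − 0.49) = 14.3. The difference detectable with 80% power is 2.80 × 14.3 × √(2/81) ≈ 6.3 points for one pair, or about 8.5 with Bonferroni over 15 pairs.

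The cost is a few sentences and no new data. The downside is that the study can no longer claim an effect of CD exercises on thoughts.
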